### Enrolment of participants

Dense sampling in Magude and Matutuine districts will be coordinated with district malaria focal points, community health workers (CHW), malaria volunteers (who provide a link between the CHW and the health facility, and assist the CHW in the follow-up of cases and administration of medication) and health facilities. All *P. falciparum* positive RDTs (i.e., SD Bioline Malaria Ag Pf, 05FK50, Abbott) will be stored for molecular analysis. RDTs of *P. falciparum*-confirmed household contacts will also be collected to estimate the rate of within-household transmission. Targeted sampling through health facility-based surveys (HFS) in low and medium-to-high transmission settings will be carried out by one team comprised of one maternal and child health nurse, a laboratory technician or a medical technician. The number of people to be screened in each health facility and the duration of recruitment to achieve the sample size will be dependent on the RDT-positivity rate among people meeting the eligibility criteria. A second test including a non-HRP2 line (StandardQ Malaria Pf/Pan Ag Test, SD Biosensor) will be carried out in HFS during the rainy season and discrepant results suggestive of *pfhrp2/3* deletions will be recorded and further analysed to confirm the deletion. Nurses at the ANC clinics will be in charge of the recruitment of pregnant women at their first visit. Pregnant women will be tested for malaria using a routine RDT and the result will be recorded in a standard questionnaire, together with routine ANC tests. Each enrolled individual will be assigned with a unique identification (UID) number and a barcode.

### Data and sample collection

Field workers and nurses will be trained to ask for informed consent (online supplemental appendix 1–4), perform a simple questionnaire (online supplemental appendix 5–8) and collect biological samples for molecular analysis. The survey questionnaire will be administered to all study participants or children’s parents/guardians meeting the inclusion criteria and will include inclusion criteria check, characteristics of the participant and malaria-related information. For pregnant participants, data will be collected on parity and gestational age at first ANC visit, as well as information related with malaria and use of preventive measures. A telephone contact number will be collected from pregnant women in low transmission settings in order to locate their residence for spatial analysis. In areas targeted by reactive surveillance activities (Magude and Matutuine in Maputo Province), travels during the previous 30 days to the case notification will be registered, including destinations and dates. A Site Coordinator will be responsible for supervising the work of field workers, nurses and the data entry clerk, and for reviewing and comparing questionnaires and samples for correct matching, completeness and accuracy.

10.1136/bmjopen-2022-063456.supp1Supplementary data

Nurses will be trained to collect blood by finger pricking (online supplemental table 1) following standard (online supplemental appendix 9) and COVID-19 safety procedures (online supplemental appendix 10). For each participant, either the *P. falciparum*-positive RDT used for routine malaria diagnosis (dense sampling) or four blood spots onto two filter papers (Whatman Grade CF 12; targeted sampling) will be collected. Specimens will be labelled anonymously (patient UID, study health facility and date), dried for 24 hours and kept in individual plastic bags with desiccants at 4°C. Every 2–6 weeks, the completed questionnaires, informed consents and samples will be sent to the data entry clerk at CISM through a local transportation agency. Informed consents will be received by study investigators. A data manager will be responsible for the receipt of the informed consents and double data entry at CISM, and a laboratory technician will be responsible for receiving the samples and store them at −20°C until analysis. Part of the dried blood spot will be stored in RNA-preserving solution. All samples will be kept in the CISM laboratory for a period of approximately 15 years. For quality control purposes, up to 5% of the samples will be analysed at UCSF (San Francisco, USA) and/or ISGlobal (Barcelona, Spain). In order to identify errors in data or sample collections and take necessary corrective actions, a standardised checklist (online supplemental appendix 11) will be filled in by the monitoring officer during biweekly monitoring visits.

10.1136/bmjopen-2022-063456.supp2Supplementary data

### Molecular analyses

Informative SNPs (including—but not restricted to—markers of resistance to artemisinin [*pfkelch13*],^37^ SP [*pfdhfr, pfdhps],*^38^ or chloroquine (*pfcrt*)^39^), microhaplotypes^40^ and *pfhrp2* and *pfhrp3* regions^6–8^ will be targeted using multiplexed primers on flanking sequences, with a range of amplicon size of ~225–275 bp (covered by a paired end read). Targeted amplicons obtained by PCR on genomic DNA using Illumina-specific adaptors and sample-specific barcode will be pooled to create a single product library, which will be sequenced (paired-end 150 bp) on a Miseq Illumina sequencer in the country or higher performing equipment when available. Amplicon representation and SNP and haplotype calling will be assessed in demultiplexed and trimmed sequencing reads after filtering sequencing errors. The designed panel will be validated using mixtures of *P. falciparum* lines to determine precision and repeatability. Genotyping methods, including number of SNPs and microhaplotypes to be characterised, distribution across the parasite’s chromosomes, the proportion of putatively neutral versus non-neutral polymorphisms, pooling strategy and criteria for validating sequencing data (ie, minimum sequencing depth and maximum error rate) will be developed as part of this project. Samples will also be used for other molecular analysis of programmatic interest, such as the detection of *Plasmodium* species, parasite antigens, serological markers of parasite exposure (antibodies) and parasite RNA-based markers (ie, gametocytes). A quality control programme based on the sequencing of an artificially created set of samples (ie, mixtures of known laboratory controls at specific proportions and densities) will be processed at predefined times to guarantee the quality of the processes during the life of the project.

### Data management

Data will be collected using paper (targeted sampling) and password-protected electronic devices (dense sampling). Data collected using paper will be double entered into the study database using RedCap.^41^ Automatic quality checks will be performed to ensure data completeness. Confidentiality and security will be ensured through automatic encryption of sensitive data, storage in password-protected computers and locked locations, and data sharing using password-protected, encrypted files. Prior to analysis, data will be deidentified with the exception of geolocation codes, which are necessary for specific analyses. The study will also use data available from the NMCP, including intervention coverage, historical prevalence surveys, travel history or other mobility assessments and entomological data. Sequences generated through the analysis of samples will be integrated into a curated catalogue of genomic data together with relevant anonymised clinical and epidemiological information and will be made publicly available in public repositories such as the European Nucleotide Archive (ENA) and MalariaGen Resource Centre. In order to facilitate data accessibility and use, and to obtain a meaningful integration with other sources of surveillance data, genetic information will be incorporated into the DHIS2-based Integrated malaria information storage system (iMISS), which is currently being rolled out in Mozambique.^42^

### Study outcomes and sample size calculations

The primary endpoints are as follows: (a) prevalence of molecular markers of diagnostic and antimalarial resistance by period, study area and population (use case 1); (b) genetic-relatedness indicators between pairs of samples and populations by period, study area and population (use case 2) and (c) genetic diversity indicators by period, study area and population (use case 3). Sample size per sampling domain (Province) has been estimated considering antimalarial and diagnostic resistance as a primary use case, considering the negligible carriage of molecular markers of artemisinin resistance^5^ and *pfhrp2/3* deletions^6^ in Mozambique, and setting 5% as the warning threshold.^43^ Assuming a 10% of loss of samples or uninterpretable analysis, a sample size of up to 500 per sampling domain would be adequate to: (a) estimate a proportion of 0.05 (markers of drug resistance or *pfhrp2* deletion) with 0.026 absolute precision and 95% confidence and (b) achieve a power of 80% for detecting an increase of genetic marker (resistance or deletion) from 0 ‰ to 5% at a two-sided p-value of 0.01. A flexible and adaptive sampling scheme will be followed, where (a) estimates generated during the first half of the project will inform subsequent sampling schemes and (b) not all the samples collected will be analysed (some of them will be stored as reference materials, for confirmation of findings or future studies on *Plasmodium* biology). The number of pregnant women to be recruited in order to reach the sample number will depend on the parasite rates in the study areas; assuming an overall RDT positivity rate of 25%, we expect we will be needing to recruit a total of 2000 pregnant women per site to get 500 *P*. *falciparum* positive samples, although numbers may differ between sites.

### Analysis plan

Demographic and clinical charateristics of study participants will be described using summary statistics. A user-friendly and locally executable bioinformatic pipeline will be developed for analysis of *P. falciparum* targeted sequencing data. Highly informative SNPs and microhaplotypes showing geographic structuring will be selected using a supervised machine learning approach trained by genomes from known geographic origin in Mozambique. Population-level genetic diversity will be quantified using expected heterozygosity (He), number of alleles per locus, allele frequency, complexity of infection (COI)^23^ as well as other genetic metrics. Deletions and copy number variations will be assessed based on sequencing coverage ratios.^10 44^ Methods to be used for population genetic analysis (including the genetic connectivity among infections, use of all vs only neutral SNPs, treatment of multiple-clone infections and integration of genetic data with travel history data) will be developed during the project. We will use regression models adjusted by potential confounders (demographic and clinical factors, among others) to compare genetic metrics between seasons, before and after the antimalarial interventions, between pregnant women and community sampling populations and across different intensities of malaria transmission. Finally, we will integrate genomic surveillance data into epidemiological and transmission network models. For the first one, we will leverage two recent models developed at the Institute of Disease Modelling^45^ (a malaria genetic model calibrated to a longitudinal genetic study in Senegal^18^ and a disease transmission model calibrated with the Magude data) to build an end-to-end malaria transmission and genetics model for Mozambique (figure 3). The transmission network model will include data for densely sampled in low transmission areas on individual and community-level case classification (imported, local and introduced), the extent and duration of sustained local transmission and how these change over space and time. Summary indicators will be visualised in graphical and tabular forms in the iMISS through genetic dashboards. We will establish risk profile algorithms and interpretation components that are capable of generating outputs on (a) country-wide antimalarial resistance profiles (rolling-basis); (b) in very low transmission areas (eg, Magude district), genetic connectivity and case classification (together with travel history and other parameters obtained from case-based notification tools) and (c) high burden to high impact specific analyses (ie, stratification and trend investigation for exploring the potential impact of intervention mixes implemented).

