**Methods and analyses:**

This prospective surveillance study seeks to generate *Plasmodium falciparum* genetic data to (1) monitor molecular markers of drug resistance and deletions in rapid diagnostic test targets; (2) characterise transmission sources in low transmission settings and (3) quantify transmission levels and the effectiveness of antimalarial interventions. The study will take place across 19 districts in nine provinces (Maputo city, Maputo, Gaza, Inhambane, Niassa, Manica, Nampula, Zambézia and Sofala) which span a range of transmission strata, geographies and malaria intervention types. Dried blood spot samples and rapid diagnostic tests will be collected across the study districts in 2022 and 2023 through a combination of dense (all malaria clinical cases) and targeted (a selection of malaria clinical cases) sampling. Pregnant women attending their first antenatal care visit will also be included to assess their value for molecular surveillance. We will use a multiplex amplicon-based next-generation sequencing approach targeting informative single nucleotide polymorphisms, gene deletions and microhaplotypes. Genetic data will be incorporated into epidemiological and transmission models to identify the most informative relationship between genetic features, sources of malaria transmission and programmatic effectiveness of new malaria interventions. Strategic genomic information will be ultimately integrated into the national malaria information and surveillance system to improve the use of the genetic information for programmatic decision-making.

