## Methods and analysis

### Study design

This is a prospective genomic surveillance study of *P. falciparum* samples to be collected between 2022 and 2023 from a variety of transmission intensities and geographies in Mozambique to inform three use cases: appropriate malaria diagnostics and treatment; characterising transmission sources in low transmission settings and identifying intervention mixes with optimal effectiveness to reduce burden in moderate-to-high transmission areas. To achieve this, three different sampling approaches will be performed. First, all malaria cases will be sampled throughout the year in two low transmission districts of southern Mozambique currently targeted by reactive malaria surveillance activities (*dense sampling*). Second, a targeted approach will aim to collect a predefined number of samples at selected health facilities in the country. In low transmission settings, sampling will be conducted throughout the year, while two surveys will be conducted in medium-to-high transmission settings: one during the rainy and a second one during the dry season (which extend from November to April and May to October, respectively). During the high transmission (rainy) season, an LDH-based RDT will be added to the standard routine HRP2-based diagnostics to identify potential false negative results due to *pfhrp2/3* deletions among clinical cases.^34^ And third, *ANC sampling* of pregnant women at first attendance will be conducted throughout the year at selected health facilities in the country. The overarching sampling strategy for the study will however remain flexible and iterative, informed by sample analysis as the study progresses, and in view of future sampling and research activities being conducted by the Ministry of Health, National Institute of Health and other stakeholders in Mozambique, to avoid sampling overlap and ensure a diversity of sampled locations.

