The project will also leverage from clinical trials and surveillance activities being conducted in Mozambique between 2021 and 2024, namely the Malaria Indicator Survey (2022–2023) in southern Mozambique; the therapeutic efficacy survey (2022) in sentinel sites in the country (Montepuez in Cabo Delgado, Moatize in Tete, Dondo in Sofala, Mopeia in Zambézia and Massinga in Inhambane);^35 36^ reactive surveillance activities in Magude and Matutuine (Maputo Province; 2022-2023); a phase III cluster-randomised, open-label, clinical trial in 2022 to study the safety and efficacy of ivermectin mass drug administration to reduce malaria transmission in Mopeia District (Zamb‘ézia Province); a large-scale implementation development project aiming at maximising the delivery and uptake of perennial malaria chemoprevention (formerly intermittent preventive treatment in infancy) in Massinga District (Inhambane Province; 2022–2024); a hybrid effectiveness-implementation study to evaluate the feasibility and effectiveness of seasonal malaria chemoprevention with sulfadoxine–pyrimethamine (SP) and amodiaquine inNampula Province (2022) and a programmatic delivery of a population-based mass drug administration with dihydroartemisinin-piperaquine in Manjacaze district (Gaza Province; 2022–2023).

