### Study settings and participants

Nine provinces were identified through consultation with the NMCP for inclusion in the study: Maputo City, Maputo, Gaza, Inhambane, Niassa, Manica, Nampula, Zamb‘ézia and Sofala. Selection of study sites will be stratified by transmission intensity into two major strata: (a) low transmission (Maputo city and Maputo Province, where individual case notification is being implemented to reach interruption of transmission) and (b) medium-to-high transmission areas (Gaza, Inhambane, Niassa, Manica, Nampula, Zamb‘ézia and Sofala provinces, targeted by burden-reducing strategies). Overall, a total of 19 districts will be included, which provide a diverse range of epidemiological settings (see table 1 and figure 2).

**Table 1 T1:** Study provinces and districts targeted in the protocol

Transmission	Region	Province	District	Sampling			
				Dense	Targeted		Other sources
					HFS	ANC	
Low	South	Maputo City	Kamavota, KaMaxaqueni and Nlhamankulu		X*		
		Maputo Province	Boane and Manhiça		X*		
			Magude	X*		X†	React
			Matutuine	X*			React
Medium-to-high		Gaza	Manjacaze		X‡	X†	MDA-DP
		Inhambane	Maxixe		X‡	X†	
			Massinga		X‡	X†	PMC and TES
	Central	Manica	Guro and Gondala		X‡	X†	
		Sofala	Chemba		X‡	X†	
			Dondo				TES
		Tete	Moatize				TES
	North	Niassa	Cuamba		X‡	X†	
		Nampula	Mecuburi, Malema, Lalaua and Muecate		X‡	X†	SMC
		Zambézia	Mopeia		X‡	X†	MDA-IVM and TES
		Cabo Delgado	Montepuez				TES

*Year round, all ages.

†Year round, first ANC visit.

‡Rainy and dry season; 2–10 years of age.

ANC, antental care clinics; HFS, health facility survey; MDA-DP, mass drug administration with dihydroartemisinin-piperaquine; MDA-IVM, mass drug administration with ivermectin; PMC, Perennial malaria chemoprevention; React, reactive surveillance; SMC, seasonal malaria chemoprevention; TES, therapeutic efficacy study.

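### The before/after comparison of genetic metrics names no concurrent comparator and has no assured baseline, so it cannot separate an intervention effect from change over time

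*Protocol article*

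**What the plan says.** The abstract (Methods and analyses) sets the third objective as to "quantify transmission levels and the effectiveness of antimalarial interventions", and the Study design section ties use case 3 to finding the intervention mixes that work best. Genetic diversity indicators by period, area and population are primary endpoint (c).

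The Analysis plan gives one regression contrast for interventions. The models will "compare genetic metrics between seasons, before and after the antimalarial interventions", as well as between pregnant women and community samples and across transmission intensities. On adjustment it says: "We will use regression models adjusted by potential confounders (demographic and clinical factors, among others". No concurrent comparison group is named. The Analysis plan and Discussion also describe joint epidemiological-genetic models as a way to assess effectiveness, again without a comparator.

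The Study design section has "samples to be collected between 2022 and 2023". In medium-to-high transmission areas the health facility surveys are one in the rainy and one in the dry season; the Table 1 footnote reads "Rainy and dry season; 2–10 years of age". First-visit antenatal (ANC) sampling is year-round in every intervention district.

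Among the studies to be drawn on is "a phase III cluster-randomised, open-label, clinical trial in 2022 to study the safety and efficacy of ivermectin mass drug administration" in Mopeia.

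**The concern.** A before/after contrast isolates an intervention only if nothing else that affects the metric changes between the two periods, or if a comparator shows what would have changed anyway. Here neither is arranged in the text. Transmission, other control measures, rainfall and the sampling scheme can all move between 2022 and 2023, and genetic diversity may move with them. At stake is whether use case 3 can say anything about which interventions work. A national programme reading an adjusted before/after difference as effectiveness could credit an intervention with an ordinary change between years, or miss a benefit that such a change masks.

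**Working it through.** **Step 1. Exposure against sampling** (Study design; Table 1). Sampling runs 2022–2023 throughout.

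| Intervention | Place | Dated | Districts |
|---|---|---|---|
| Ivermectin MDA | Mopeia | 2022 | 1 |
| PMC | Massinga | 2022–2024 | 1 |
| MDA-DP | Manjacaze | 2022–2023 | 1 |
| Seasonal malaria chemoprevention (SMC) | Nampula | 2022 | 4, in one row labelled SMC |

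Every intervention is dated from the first sampling year. Months are not given, so some pre-intervention sampling is possible but nothing secures it. The older biorepository is cited for marker selection, not as a baseline.

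**Step 2. Identification.** In one district, write the mean metric as base level + time effect + intervention effect. The before/after difference estimates (time + intervention). An indicator for period is the same column as an indicator for intervention, so adjusting for period removes the contrast, and not adjusting leaves the time effect in. Demographic and clinical covariates correct for a changed case mix, not for district-wide change. The open covariate list therefore does not help. Because the Sample size section lets first-half estimates reshape later sampling, sampling itself may also differ between periods.

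**Step 3. Season.** If the rainy and dry facility surveys fall on either side of an intervention's start, period and season coincide as well. Year-round ANC sampling is less affected.

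**Step 4. The plan's own sample size.** It is built on resistance and deletion markers. For 0 versus 5%, two-sided 0.01, 80% power:

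- n per group = [2.576·√(2·0.025·0.975) + 0.842·√(0.05·0.95)]² / 0.05² = 227, so 454 in two groups.
- With 10% loss: 454/0.9 = 505, or 454 × 1.1 = 500. The stated figure of up to 500 per Province reproduces.

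It does not size a before/after comparison of diversity metrics. For illustration, 500 × 0.9 = 450 evaluable samples, or 225 in each of two periods.

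**Step 5. What an uncontrolled test would do.** The documents give no size for drift, so the values of s below (in SD) are assumptions. With no true effect, u = s/√(2/n) and P(significant at 0.05) = Φ(u − 1.96) + Φ(−u − 1.96).

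| Drift s | n = 112 per period | n = 225 | n = 450 |
|---|---|---|---|
| 0 | 5% | 5% | 5% |
| 0.05 | 7% | 8% | 12% |
| 0.1 | 12% | 19% | 32% |
| 0.2 | 32% | 56% | 85% |
| 0.3 | 61% | 89% | 99% |

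The 112 column is a Province total shared by two districts, as Massinga shares Inhambane with Maxixe (225/2). More samples make the false signal more likely.

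**Step 6. What a comparator buys and costs.** If the comparison district shares the same trend, a difference-in-differences returns the false-positive rate to 5%. The detectable difference (80% power, two-sided 0.05) is 2.80·√(2/n) for before/after and 2.80·√(4/n) for difference-in-differences:

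| n per cell | Before/after | Difference-in-differences |
|---|---|---|
| 225 | 0.26 SD | 0.37 SD |
| 450 | 0.19 SD | 0.26 SD |

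**Step 7. What it does not buy.** If each district also has its own independent shift per period with SD t, the true variance is 2/n + 2t² for before/after and 4/n + 4t² for one district against one. The ratio of assumed to true variance is the same, so the false-positive rate is the same: at n = 225 and an assumed t = 0.1, 2·[1 − Φ(1.96·√(0.00889/0.02889))] = 28%. One treated against one comparison district removes shared change only.

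**The case against.** The strongest reply is that the article is condensed, that silence about comparators does not mean they will go unused, and that endpoint (c) is already defined by area and period, which is the structure a controlled contrast needs. That is fair, and the most that can be said is that comparators are not named. It does not remove the point, because the contrast that is named is the weak one.

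Several stronger readings are tempting and are not supported:

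- *Season will be taken for an intervention effect.* The Analysis plan treats season as a comparison of its own, ANC sampling is year-round, and start months are unknown. The overlap is conditional and concerns mainly the facility surveys.
- *Effectiveness rests on these regressions alone.* The joint models are a second route, supported by coverage, historical prevalence and entomological data. They still have no named comparator.
- *Standard errors will be computed at individual level.* The article specifies neither the unit nor the variance method.
- *Surveyed children in Massinga are outside the PMC target age.* The article says only that PMC was "formerly intermittent preventive treatment in infancy"; it gives no current age range.
- *Maxixe is an intervention-free control.* Its blank cell is under linked data sources, which is not a statement about exposure.

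It is also true that resistance and deletions, on which the study is sized, are untouched, and that the article itself says more evidence is needed before genetic data are used to assess interventions. That caveat is about whether the metrics track transmission; it does not deal with confounding by time.

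**Conclusion.** The point holds in a limited form. The article states an uncontrolled before/after contrast, with no assured baseline, for an aim worded as effectiveness. For the three single-district interventions, calendar change cannot be separated from effect at any sample size. For SMC there are four districts, but they share one Province and one label, and no comparator is named.

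The structural argument needs no assumption beyond the dates and Table 1. The size does: false-positive rates of 19% to 56% at 225 per period rest on an assumed drift of 0.1 to 0.2 SD, equal split of a full Province sample and a normal approximation. This is a cheap improvement to one of three use cases, not a defect in the study as a whole.

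**What to change.** In the Analysis plan:

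1. **Mopeia.** Compare genetic metrics between the ivermectin trial's randomised clusters, with cluster as the unit or as a random effect. Make sure each sample can be linked to its cluster. The article has specimens labelled with participant number, facility and date, and mentions locating residence only for pregnant women in low transmission settings; the questionnaires are not shown.
2. **Massinga, Manjacaze and Nampula.** Use season-matched difference-in-differences (rainy with rainy, dry with dry, or ANC samples by calendar month) against concurrently sampled districts with no listed intervention: for example Maxixe, Guro, Gondala, Chemba or Cuamba. First check their intervention status against the national programme's coverage data. Only Maxixe shares a Province with its treated district, so the parallel-trend assumption is weaker elsewhere.
3. **Wording.** Label the contrasts in item 2, including Massinga against Maxixe, and any uncontrolled before/after result as descriptive, not as effectiveness. Name the comparator for the joint models too.

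The cost is text and possibly one linkage field. Matching facility surveys by season needs each season surveyed both before and after the start; the article does not say the surveys are repeated, and where they are not, the ANC stream is the one to use. Intervals widen as shown in step 6, and the claims become weaker.
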